## Abstract

**Background:**

Lifestyle factors playing a role in the development of late-life disability may be modifiable. There is a need for robust evidence about the potential for prevention of disability through behavior change interventions.

**Methods/design:**

This feasibility study involves the development, implementation and initial testing of a behavior change intervention in a naturalistic setting. A small-scale randomized controlled trial (RCT) will investigate the implementation of a goal-setting intervention aimed at promoting behavior change in the domains of physical and cognitive activity in the context of a community resource center for over-50s. Healthy older participants attending the center (*n* = 75) will be randomized to one of three conditions: control (an interview involving a general discussion about the center); goal-setting (an interview involving identification of up to five personal goals in the domains of physical activity, cognitive activity, diet and health, and social engagement); or goal-setting with mentoring (the goal-setting interview followed by bi-monthly telephone mentoring). All participants will be reassessed after 12 months. Primary outcomes are levels of physical and cognitive activity. Secondary outcomes address psychosocial (self-efficacy, mood, quality of life), cognitive (memory and executive function), and physical fitness (functional and metabolic) domains. Cost-effectiveness will also be examined.

**Discussion:**

This study will provide information about the feasibility of a community-based lifestyle intervention model for over-50s and of the implementation of a goal-setting intervention for behavior change, together with initial evidence about the short-term effects of goal-setting on behavior.

**Trial Registration:**

Current Controlled Trials ISRCTN30080637 (http://www.controlled-trials.com)

## Background

Older people are living longer and form a greater proportion of the population than ever before. It is important to identify ways of promoting good health and preventing, delaying, or reducing the severity of age-related cognitive and physical disability, in order to enhance or maintain independence, wellbeing, and quality of life (QoL) for older people and limit the social and economic burden of care and support [1,2].

Multiple factors are involved in the pathway to age-related cognitive and physical disability. While some are not readily modifiable (for example, Apo-E status), lifestyle factors offer potential for change [3]. Increased levels of cognitive activity (CA) and physical activity (PA), and engagement in socially-oriented leisure activity, are associated with maintenance of cognitive function and reduced risk of Alzheimer’s disease [4]. Increased levels of PA contribute to improved physical functioning and health, help to combat depression, and decrease the risk of falls and cardiovascular disease. Theoretically it is suggested that engaging in such activities creates greater cognitive reserve and hence greater resilience in relation to age-related brain pathology [5]. Since many older people are socially isolated and cognitively and physically under-active [6,7], there is an urgent need for robust evidence regarding the potential for effective health promotion and prevention with regard to lifestyle factors. It is now timely to begin to test interventions addressing these factors in randomized controlled trials (RCTs) with long-term follow-up [4,8].

The complex range of factors involved indicates a need to address multiple risk factors in an integrated manner [4]. PA and CA trials have typically involved practice of circumscribed skills for a defined period, producing improvements in trained skills but little evidence of transfer of gains or long-term behavior change. Lifestyle activities, in contrast, can be characterized as the active co-ordination of multiple complex cognitive and physical abilities with the function of attaining personally-meaningful goals. Increasing CA and PA through lifestyle activity can ensure that changes are integrated into everyday life, stabilizing functioning and improving ability to cope with future challenges to wellbeing.

We aim to establish the feasibility of an innovative approach to increasing CA and PA among over-50s, including ‘hard to reach’ groups, based on goal-setting. Setting oneself stimulating but achievable goals is an effective means of changing behavior [9], providing motivation to perform better or maintain effort. The social cognitive theory of health behavior change [10] posits that this is most effective where perceived self-efficacy is such that the individual believes it is possible to achieve the desired effects through his/her own actions, and where adopting different behaviors proves enjoyable and socially-rewarding and enhances self-worth. Behavior change is most likely where the environment supports implementation of the desired behavior [11] through availability of peer support and accessibility of facilities and opportunities that can be matched with personal goals, and provides a means of overcoming perceived obstacles. In line with social cognitive theory, we will examine the benefits of developing a context that provides social and material support for behavior change, and of using a goal-setting intervention, with or without follow-up mentoring aimed at boosting self-efficacy and encouraging problem-solving regarding obstacles to change, to optimize use of this resource compared to simple access to facilities. We hypothesize that goal-setting, especially when accompanied by ongoing mentoring, will optimize engagement, leading to increased CA and PA, with benefits for cognitive, physical, social and psychological functioning, health, and QoL.

## Method

### Design

This is a feasibility study involving the development, implementation and initial testing of a naturalistic lifestyle intervention. A small-scale randomized controlled trial (RCT) will investigate the implementation of a goal-setting intervention aimed at promoting behavior change in the domains of PA and CA in the context of a community resource centre for over-50s. We will explore the acceptability of the approach (for example, willingness to participate and be randomized; attrition rates), its success in reaching those sections of the older population most in need and realizing its socially-inclusive ethos, and the age and demographic profile of those interested in engaging. We will examine the suitability of potential outcome measures, and use the findings to estimate critical parameters to inform the design of a large-scale RCT. A CONSORT-style flowchart is provided in Figure 1. The study has been approved by the relevant University and National Health Service Research Ethics Committees. This trial is registered with Current Controlled Trials, reference ISRCTN30080637.

**Figure 1 F1:**
[figure not shown]
AgeWell Study CONSORT-style flowchart.

### Participants

All individuals aged over 50 years living in the local community and attending the community resource center will be invited to participate, with no exclusions. If they do not wish to take part in research they may still attend the center, and in this case only records of attendance and activity participation will be taken. Sample size calculation for this feasibility study is based on anticipated attendance rates. We expect to randomize at least 75 individuals (target *n* = 25 per condition). Reasons for declining to participate will be recorded where given, although participants are not required to give this information. Attrition at any stage will be noted and reasons recorded where available, although participants are free to withdraw without giving a reason.

### Intervention

The intervention is conducted in partnership with Age Cymru Gwynedd a Môn (ACGM). Age Cymru is a registered charity within the devolved nation of Wales which forms part of Age UK, a major voluntary sector organization working to improve later life through provision of services and support throughout the UK [12]. ACGM provides services and support in the counties of Gwynedd and Anglesey in north-west Wales. The development of a community resource center for over-50s (‘AgeWell Centre’) will provide the context for the intervention, which compares the effects of three different styles of interview on subsequent behavior change.

The AgeWell Centre will be established in the village of Nefyn, Gwynedd, building on the experience of ACGM in setting up and running successful community-based facilities for over-50s in Anglesey, supported by a knowledge transfer partnership focused on physical activity, with several hundred beneficiaries over the past 2 years. A coordinator will facilitate the running of the center, supported by a volunteer management group of center attendees. The center will open 3 days a week to provide a range of activities that address the need for increased CA and PA and encourage adaptive health-related behavior around a central core of social interaction. Specific activities addressing the key areas in which behavior change is desired will be offered, targeting moderate to high intensity PA (walking, resistance training, tai chi) and CA (memory management, computing skills, reading group, creative writing, local history). Other activities will be developed and offered according to participant interest and need, for example, cooking for one, dancing, photography, gardening, community volunteering, and outings. Each activity will either be delivered by an outside facilitator or planned and carried out by a group of center participants. Participants will pay a nominal fee for all sessions, covering the costs of bringing in outside facilitators. The center will offer resources such as computers with internet access and fitness equipment. The center will also host a falls prevention group and offer a focus for community-based provision by other agencies. Records of attendance and participation for all those coming to the center will be compiled using the CharityLog database.

Those center attendees willing to participate in the RCT will be randomly allocated using a sequentially-randomized dynamic adaptive computer algorithm developed by the trials unit (NWORTH) and incorporating stratification by gender to one of three conditions following initial assessment [13]. Each condition involves a one-to-one interview with an appropriately-trained professional, lasting up to 1.5 h, as follows:

1. Group 1, control, will have a general discussion about the facilities and activities available.

2. Group 2, goal-setting, will have a structured goal-setting interview using the Bangor Goal-Setting Interview. The interview will explore current functioning in relation to PA and CA, as well as considering social engagement, diet, and health. The interviewer will have access to key information from the initial assessment such as details of identified health risks. Areas where the participant would like to make changes or improvements will be identified and prioritized, and up to five specific, realistic and achievable goals will be identified. Examples of goals might be increasing walking to 30 min per day, or learning to use email to communicate with a friend. Current performance, satisfaction with performance, and degree of confidence in carrying out the activity, will be rated by the participant on a scale of 1 to 10. Behavioral indicators of partial (25%, 50%, 75%) and complete goal attainment will be established for each goal. Ways in which the goal may be addressed will be discussed and linked to center activities (for example, walking group, computer skills sessions) or external facilities (such as, GP consultation, smoking cessation group), and a written individual action plan will be prepared.

3. Group 3, goal-setting with mentoring, will receive the same interview as Group 2 plus a follow-up mentoring phone call from the interviewer after 1 month (in month 2 of participation in the study) and then bi-monthly thereafter (in months 4, 6, 8, and 10) to review progress, problem-solve regarding any obstacles to progress, encourage and reinforce successes, and support maintenance of change. Each participant will remain in the study for 12 months, and will engage according to personal choice in center and related activities. Attendance and activity participation will be recorded. All participants will be reassessed after 12 months by a researcher blind to group allocation. At follow-up assessment, participants will re-rate performance and satisfaction with regard to each identified goal, and a rating of goal attainment will be made.

The Bangor Goal-Setting Interview, developed by the research team, provides a structured format for the goal-setting process. This interview is similar in some respects to the format of the Canadian Occupational Performance Measure [14], a well-established clinical method for measuring performance in a standardized manner across different individual goals [15], which has proved to be a sensitive measure of change in previous rehabilitation research [16]. However, it derives from a different theoretical model, incorporates a number of different features, and has been developed primarily as a research tool. The Bangor Goal-Setting Interview is based on the social cognitive theory of behavior change [10] and on the concept of motivational interviewing [17]. The interview structure allows researchers to select areas of behavior that are relevant to the aims of the study; for the present study we have selected the four areas of physical activity, cognitive activity, diet and health, and social engagement. The interview proceeds in three stages. Firstly, each of these areas is discussed in turn with a view to eliciting issues that might form the basis for behavioral goal-setting. For each area, the participant rates perceived importance of making changes in this area, and readiness to make changes in this area, on a scale of 1 to 10 (where 1 is not at all important/not at all ready and 10 is extremely important/completely ready). Once all areas have been discussed, the second stage involves revisiting each area in turn and negotiating specific behavioral goals that conform to SMART principles (specific, measurable, achievable, realistic, and time-delineated). For this study, we specified that two to five goals should be set, and that these could be in any of the four areas covered. Once a goal is set, and current performance described, possible barriers and facilitators to achieving the goal are discussed using specific prompts, with an emphasis on identifying the resources available to support behavioral change. Additionally, goal attainment indicators are specified, providing clear descriptors of what would constitute 25%, 50%, and 75% goal attainment. In the final stage of the interview, the participant is asked to rate, for each of the goals that have been identified, current performance and satisfaction with performance on a scale of 1 to 10 (where 1 is unable to perform/extremely dissatisfied and 10 is able to perform perfectly/extremely satisfied). Mean scores for performance and satisfaction with performance across goals are calculated by dividing in each case the sum of the scores for all goals identified by the number of goals set. At follow-up, the participant re-rates current performance and satisfaction with performance for each goal so that changes in ratings can be examined. The interviewer elicits information about current performance and uses the previously-specified goal attainment indicators to determine the extent of progress towards achieving the goal. Within the interview schedule there is scope to elicit informant ratings of performance and descriptions of goal attainment, for comparison purposes; this is particularly relevant for example where respondents have cognitive impairments. Similarly, assessor ratings can be made where the assessor has been involved in a therapeutic or supportive capacity in helping the participant work towards selected goals. As the present study involves healthy older participants, only self-ratings will be elicited.

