#### *Process measures*

Data on attendance at the Centre and participation in Centre activities will be examined for participants in all three groups.

For groups 2 and 3, changes in goal performance and satisfaction ratings, and the extent of goal attainment, will be assessed.

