### Procedure

Individuals attending the Centre will be given information about the study and invited to consider participating in the trial by a member of the research team, after which they will be given as much time as they need to decide whether they wish to take part. Those who consent to participate will complete the baseline assessment in two face-to-face sessions with a researcher, one focusing on psychological, social and cognitive measures and lasting approximately 1.5 h, and the other focusing on physical health and fitness and lasting approximately 1 h. The researcher will then trigger the randomization. Participants will be allocated to one of the three conditions and will engage in the interview conducted according to the protocol for their allocated condition. Those in the goal-setting with mentoring group will have bi-monthly mentoring phone calls from the interviewer over the following 12 months while the remainder will have no such contact. After 12 months all participants will engage in a follow-up interview in accordance with the condition to which they were allocated; for participants in the goal-setting and goal-setting with mentoring groups the interviewer will use the Bangor Goal-setting Interview to elicit current ratings of performance and satisfaction with performance for the originally-identified goals, while those in the control group will have a general discussion with the interviewer. The interviewer will then trigger the follow-up assessment and all participants will be reassessed by blinded members of the research team.

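### Goal attainment at 12 months is determined by an interviewer who knows the arm and mentors Group 3 only, so a Group 2 versus Group 3 difference in this process measure is open to differential rater bias

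*Protocol article*

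**What the plan says.** All references are to the protocol article.

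- **Who determines attainment.** The Intervention section, in its account of the Bangor Goal-Setting Interview, says that at follow-up the interviewer asks about current performance and "uses the previously-specified goal attainment indicators to determine the extent of progress towards achieving the goal". The indicators are descriptors of 25%, 50% and 75% attainment, written when each goal is set.
- **Who mentors.** The Group 3 description in the Intervention section adds to the goal-setting interview a "follow-up mentoring phone call from the interviewer" after 1 month, with further calls in months 4, 6, 8 and 10. The Procedure section agrees: "Those in the goal-setting with mentoring group will have bi-monthly mentoring phone calls from the interviewer over the following 12 months". Groups 1 and 2 have no such contact.
- **Who conducts the 12-month goal interview.** In the Procedure section the follow-up interview is run by allocated condition. For Groups 2 and 3, "the interviewer will use the Bangor Goal-setting Interview to elicit current ratings of performance and satisfaction with performance". The interviewer then sets off a separate reassessment by blinded staff.
- **The other wording.** The Group 3 paragraph of the Intervention section states: "All participants will be reassessed after 12 months by a researcher blind to group allocation". Its next sentence places the goal re-ratings and the attainment rating at the follow-up assessment and names no rater.
- **Status of the measure.** Under Process measures, for Groups 2 and 3, "changes in goal performance and satisfaction ratings, and the extent of goal attainment, will be assessed". The Data analysis section specifies the Group 2 versus Group 3 contrast for cognitive and physical activity, not for attainment.

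**The concern.** Attainment requires a judgement: someone must map a participant's account of current performance onto a percentage step. On the detailed text, that person knows the allocation, helped to write the indicators and, in Group 3 only, has spent the year encouraging the participant towards those goals. The conditions for leniency therefore differ between exactly the two arms in which attainment is measured. If Group 3 scored higher, the data could not show whether mentoring helped or the mentor scored generously.

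This matters because the study is meant to examine candidate outcome measures and to use its process data in preparing a definitive trial. A rating procedure with this weakness could be carried forward. In addition, a reader of the Group 3 paragraph alone could believe that attainment was rated blind.

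**Working it through.** The document gives no figure for attainment (no SD, expected difference or test), so there is nothing to reproduce. The check is mainly a comparison of passages.

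**Step 1: rater and order**

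| Question | Intervention, Group 3 paragraph | Intervention, account of the goal interview | Procedure |
|---|---|---|---|
| Who determines attainment? | Not named | The interviewer | The interviewer conducts the goal interview; attainment is not mentioned |
| When? | At the follow-up assessment, directly after the statement on blinded reassessment | At follow-up | The goal interview comes before the blinded reassessment |
| Does that person know the arm? | Implied not, if the rating belongs to the blinded reassessment | Not stated | Yes: the interview is run by condition |
| Who mentors Group 3? | The interviewer | Not addressed | The interviewer |

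The wording that names a rater names the interviewer, and the wording that gives the order of events separates the goal interview from the blinded reassessment. Only the unattributed sentence in the Group 3 paragraph points the other way.

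**Step 2: what is and is not the interviewer's judgement**

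Performance and satisfaction are re-rated by the participant, who knows whether they were mentored. Changing the data collector cannot blind those ratings. Attainment is the component that the interviewer determines.

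**Step 3: scale, by assumption only**

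From the Participants section: target n = 25 per condition (3 × 25 = 75, as stated). Everything else in this step is assumed.

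- *Inflation.* Suppose one 25-point step is over-scored for 10%, 20% or 30% of Group 3 goals and for none in Group 2. Mean inflation is the share × 25: 0.10 × 25 = 2.5, 0.20 × 25 = 5 and 0.30 × 25 = 7.5 points. With an assumed SD of 25 to 30 points, the range is 2.5/30 = 0.08 SD to 7.5/25 = 0.30 SD.
- *Precision.* With no dropout, the 95% half-width for 25 versus 25 is 1.96 × √(2/25) = 0.55 SD.
- *False-positive rate, if attainment were tested.* With no true difference, a pure bias of b SD and SE = √(2/25) = 0.283, the two-sided 5% rejection rate is Φ(b/SE − 1.96) + Φ(−b/SE − 1.96):

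| b (SD) | Rejection rate |
|---|---|
| 0 | 5% |
| 0.1 | 6% |
| 0.2 | 11% |
| 0.3 | 19% |
| 0.5 | 42% |

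These rates show only what a given bias would do. They are no evidence that a bias of any particular size exists.

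**The case against.** The strongest reply is that little depends on this comparison. Attainment is a process measure in a feasibility study, no between-arm test of it is stated, and the outcomes that carry the planned contrasts are reassessed blind. Indicators fixed in advance narrow the rater's discretion. All of this stands and limits the weight of the point. It does not remove the bias, because placing a reported performance on a step still takes judgement.

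Several stronger readings are tempting, and the document does not support them:

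- *That rater bias in attainment reaches the primary or secondary outcomes.* It does not: blinded staff reassess those in a separate step.
- *That attainment and goal ratings are the only process evidence on mentoring.* Centre attendance and activity participation are also process measures, recorded in all three groups.
- *That the mentor also scores performance and satisfaction.* Those are self-ratings. A wish to please the mentor is possible, but that is a different problem.
- *That restricting ratings to the participant's own contradicts the interviewer's role.* In context, that sentence excludes the optional informant and assessor ratings. It does not withdraw the interviewer's determination of attainment.
- *That the sections flatly disagree on the rater.* The Group 3 paragraph names nobody, so it is ambiguous rather than an opposing statement.

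It is also inferred, from the repeated reference to the interviewer, that one individual sets the goals, mentors and rates. Even if a different person rated, the 12-month interview is run by condition, so that person would still know the arm.

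Finally, giving the goal records to the blinded researcher carelessly could do harm. Controls have no goals, so seeing the records early would reveal Group 1 versus Groups 2 and 3 before FCAS and PASE are collected. That objection is sound, and the fix must meet it.

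**Conclusion.** The point holds, limited to goal attainment in Groups 2 and 3. The procedure as described has attainment determined by someone who knows the arm and mentors one of the two arms, while one paragraph can be read as promising a blinded rating. A Group 2 versus Group 3 difference in attainment is therefore open to differential rater bias and cannot by itself support a conclusion about mentoring.

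The size of the bias cannot be obtained from the document. The 0.08 to 0.30 SD range rests entirely on the assumed share of goals over-scored, the one-step error confined to Group 3, and the assumed SD. It lies inside the 0.55 SD half-width, so it should not be read as an estimate. No figure in the protocol changes.

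**What to change.** Reconcile the Group 3 paragraph, the account of the goal interview (both in the Intervention section) and the Procedure section, so that they name one rater and one order:

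1. Attainment alone is scored against the written 25/50/75% indicators by a researcher blind to Group 2 versus Group 3. This can be done from the interviewer's written record of current performance with mentoring references removed, or directly with the participant at the very end of follow-up.
2. That researcher does not see the goal records until FCAS, PASE and all other outcomes are complete in every follow-up session. Baseline assessment takes two sessions; if follow-up does too, the end of the first session is too early.
3. Performance and satisfaction stay as participant self-ratings and are described as such.

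If this is not adopted, state that attainment is rated unblinded, report it descriptively by group, and draw no inference from it about the benefit of mentoring.

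The cost is a few extra minutes, with no new staff or visit. After outcomes are complete, the scorer learns that goals were set, and so Group 1 versus Groups 2 and 3 status. Participants may still mention the calls, and a record written by the interviewer may still carry the interviewer's view. The change therefore reduces the bias without guaranteeing its removal.
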